#### ML Methodology

State-of-the-art ML algorithms are used to analyze labeled gameplay data. Specifically, we attempt to classify game-generated data based on the user’s known label (ADHD or non-ADHD). All in-game events of a gameplay session are recorded to form a time series that one can use to reconstruct the whole gameplay session. These events correspond to player actions and environmental parameters, such as performing a jump/move, left or right moving action, obstacle collision, and coin collection. Informative feature extraction is performed by splitting players’ time series depending on the game level. Different feature extraction techniques are assumed for each level depending on its type. In the main runner game, several aggregates are calculated by capturing different events during the gameplay (ie, movement of a player or the ability to avoid obstacles). In the mini games, feature extraction is based on the characteristic game mechanics and events of the respective mini game. The final feature vector of each player is produced by concatenating the individual-level feature vectors.

A schema that includes train-test splitting with a 75:25 split ratio, *k*-fold cross-validation (CV) with k=3, an ML pipeline, and data evaluation was designed for experimental purposes. The train-test splitting is used for model specification (eg, feature selection and model tuning), model selection, and training of the final model. Modeling decisions are made on the training set. Thus, the test set is used only to evaluate and report the statistics of the algorithm’s performance. The purpose of 3-fold CV is to fine-tune the hyperparameters of the supervised learning algorithms (classifiers) that we investigate.

For each classifier, an ML pipeline was designed to include the following procedures: (1) removal of features with 0 variance, (2) univariate feature selection according to a statistical criterion (ANOVA *F* value between label and feature), (3) principal component analysis for dimensionality reduction, and (4) classifier training. Therefore, the hyperparameters of all the steps are tuned (eg, the number of components in principal component analysis) in the 3-fold CV process. The *F1* score is used as the optimization criterion in the 3-fold CV, and the best configuration of each method's pipeline is then used on the entire training set (fully trained pipeline).

Next, the algorithm with the best-performing pipeline in the 3-fold CV is selected as the proposed method. The general performance of our system on unlabeled data is estimated by evaluating the predictive performance of the proposed method that consists of a fully trained pipeline on the test set. The performance of the ML system is also evaluated based on methods other than the proposed one. The following learning algorithms were applied: k-nearest neighbors (kNN) [37], logistic regression (LogReg) [38], support vector machine (SVM) [39], random forest (RF) [40], ridge classifier (RC) [41], passive aggressive classifier (PAC) [42], stochastic gradient descent (SGD) [43], and naïve Bayes (NB) [44]. For each classifier, we tuned its most important parameters using grid-search CV on a sufficient range of parameter values. The objective of the optimization is to maximize the micro-*F1* score across all validation folds. In addition, we report the performance metrics of accuracy, precision, recall, and *F1* scores.

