### Gameplay Data

Following the methodology described above, we present the results of a preliminary analysis of gameplay data collected during pilot trials. Gameplay data were collected from all recruited participants. However, technical difficulties (ie, unstable internet connection and game installation issues) led to insufficient or no data generation in 13 of the 43 participants (30%). Therefore, gameplay data collected from 30 (70%) participants were used in the following preliminary analysis. We comprehensively describe the CV results for a training set consisting of data collected from 22 of the 30 participants (73%) as well as the selection of the best model. Subsequently, we evaluate the predictive performance on a test set consisting of data gathered from 8 (27%) participants using point estimates and CIs.

A graphical illustration of the CV *F1* results for each learning method is shown in Figure 2. Furthermore, detailed results of the *F1* score and the other performance measures for the CV procedure are given in Table 3.

Most classifiers achieved an *F1* score above 0.5. We observed significant overfitting for RF, kNN, and NB, with a difference of 0.1 between the training and validation scores. The test performance scores are given in Table 4.

The previously mentioned models seem to be substandard solutions for this classification problem, with all of them dominated by LogReg, SGD, SVM, and PAC. The latter models feature a tradeoff between validation performance and goodness of fit. Among these methods, we selected SVM for the following reasons: (1) It achieves the highest validation *F1* score (0.66). (2) Although SGD achieves the same validation score as SVM, the latter also achieves a better fit with a difference of approximately +0.07 between training and validation, which is approximately –0.09 for the former.

Even though the results are indicative of the potential that ML has in the domain of ADHD prediction based on gameplay data, we presume that experimenting with a larger data set could give more accurate and concrete conclusions.

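### Performance rests on one 75:25 split of about 30 children, so the headline accuracy of 0.85 (6 of 7 by the tables) is imprecise and depends on the split; repeated nested cross-validation should be the primary estimate

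*Protocol article*

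**What the plan says.** The ML Methodology section of the protocol article describes "A schema that includes train-test splitting with a 75:25 split ratio". All modelling decisions are confined to the training part. On the inner loop it says: "The purpose of 3-fold CV is to fine-tune the hyperparameters of the supervised learning algorithms (classifiers) that we investigate". The same inner loop selects among eight algorithms, each with its own pipeline of feature selection, principal component analysis and grid search. On the held-out part it says that "the test set is used only to evaluate and report the statistics of the algorithm’s performance". No repetition of the split, outer cross-validation loop or pooling over splits is described.

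In the Gameplay Data section, "gameplay data collected from 30 (70%) participants were used in the following preliminary analysis". The training set is given as 22 children, and performance is evaluated on a "test set consisting of data gathered from 8 (27%) participants using point estimates and CIs". Table 4 gives the selected SVM a test accuracy of 0.85 with an interval of 0.71 to 1.00. The Abstract and Discussion present this as high performance and a marked ability to tell the two groups apart.

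**The concern.** With about 30 children, a quarter held out is 7 or 8, and each tuning fold holds about 7. A proportion read from one draw of that size moves in large steps and depends heavily on which children fall into the draw. About three quarters of the children never contribute to the reported test estimate.

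At stake is the main claim for the detection goal. The article proposes the platform as a complementary screening tool for children on the strength of this one figure. It says that a larger data set would help, but it does not discuss dependence on the split, which can be reduced with the children already enrolled.

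**Working it through.** **1. The stated split.** 30 × 0.25 = 7.5, rounded to 8 test and 22 training children, as the text says. Per tuning fold: 22/3 = 7.3.

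**2. Denominators implied by the tables.** These are back-calculated, not stated in the article.
- Table 4 test accuracies are 0.28, 0.42, 0.57 and 0.85. They match 2/7, 3/7, 4/7 and 6/7 cut to two decimals. None is a multiple of 1/8 (0.25, 0.375, 0.50, 0.625, 0.75, 0.875).
- Table 3 validation accuracies are 0.4286, 0.5238, 0.5714, 0.6190 and 0.6667. They match 9, 11, 12, 13 and 14 out of 21. None is k/22.
- Check on the SVM row of Table 4: recall 1.00 and precision 0.75 fit 3 true positives and 1 false positive. With 3 true negatives, accuracy is 6/7 = 0.857 and F1 is 2 × 0.75 × 1.00/1.75 = 0.857, both as printed.

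The tables therefore imply 21 + 7 = 28 children, against 22 + 8 = 30 in the text.

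**3. Precision of the headline.** 6/7 = 0.857, and one child is worth 1/7 = 0.14. The exact (Clopper-Pearson) 95% CI for 6/7 is 0.42 to 0.996, much wider than the printed 0.71 to 1.00, for which the article gives no level or method.

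Probability of at least 6 correct out of 7:
- 0.12 if true accuracy is 4/7 (the majority class);
- 0.26 if true accuracy is 2/3 (the SVM's own cross-validation value).

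**4. Effect of the split alone.** Assume that 20 of 28 children are classifiable whatever the training set (14 of 21 in validation plus 6 of 7 in the test set). Drawing 7 at random is hypergeometric with p = 20/28 = 0.714:

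SD = √[p(1 − p)/7 × (28 − 7)/(28 − 1)] = √[0.2041/7 × 21/27] = 0.15.

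The central 95% range of test accuracy over splits is 3/7 to 7/7, that is 0.43 to 1.00.

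**5. Gain from evaluating every child.** Approximate half-width, 1.96 × √[p(1 − p)/n] at p = 0.714:
- n = 7: 0.33;
- n = 28: 0.17.

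Both are normal approximations. At n = 7 the upper limit exceeds 1 (0.714 + 0.33 = 1.04). At n = 28 the formula treats out-of-fold predictions as independent, which they are not, because the training sets overlap.

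**6. What would remain uncertain.** Pooling the SVM's validation and test results gives (14 + 6)/28 = 0.71, exact 95% CI 0.51 to 0.87. This is only a guide: the 14 were used in selection, and the fold models were trained on fewer children than the final one. The majority-class rate is 12/21 = 4/7 = 0.57, which lies inside the interval.

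**The case against.** The strongest defence is that the design is sound against leakage. Modelling decisions stay on the training set, the SVM was chosen on cross-validation, and the test set was kept for reporting. The article calls the analysis preliminary, prints intervals and asks for more data. This stands: a reader might infer that 0.85 is a biased figure, and the documents do not support that. They do support that it is imprecise and depends on the draw, which the caveat about sample size does not address.

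A reader might also take the shifts between Tables 3 and 4 as proof against the splitting method. They are not:
- SVM goes from 0.67 to 0.85. At a true accuracy of 2/3, the chance of 6 or more out of 7 is 0.26.
- SGD goes from 0.67 to 0.42. At the same true accuracy, the chance of 3 or fewer out of 7 is 0.17. Neither move is unusual for 7 children.
- Logistic regression has zero recall in training and validation and full recall in the test set. This could equally be a degenerate fit or an implementation problem, and the documents do not allow it to be attributed to the split.

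Finally, nested cross-validation does not estimate quite the same thing. The article's target is one fully trained pipeline, whereas nested cross-validation describes the whole procedure, including the choice of algorithm. That is a real difference and has to be stated when the result is reported.

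**Conclusion.** The concern holds as one of precision and split-dependence. The single performance estimate rests on 7 children by the tables (8 by the text). Its exact 95% CI runs from 0.42 to 0.996, and the draw of test children alone contributes an SD of about 0.15.

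The counts of 28, 21 and 7 are inferred from the tables. With 8 test children the approximate half-width would be 0.31 instead of 0.33, so the conclusion does not depend on which count is right. The SD of 0.15 rests on the assumption that 20 of 28 children are classifiable irrespective of the training set.

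It would be tempting to conclude that a better validation scheme would settle whether the game discriminates. The figures do not support that. Using every child removes most of the split noise and roughly halves the error, but it adds no children, and the pooled interval of 0.51 to 0.87 still contains the majority rate of 0.57.

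**What to change.** - Reconcile the 22 and 8 children in the text with the 21 and 7 implied by Tables 3 and 4.
- Make participant-level, stratified, repeated nested cross-validation the primary performance estimate (for example 5 outer folds, 3 inner folds, at least 50 repeats). Feature selection, principal component analysis, tuning and the choice among the eight algorithms all belong inside the outer loop.
- Report out-of-fold sensitivity, specificity and balanced accuracy. Use an interval that allows for dependence between folds and repeats, for example a bootstrap that resamples children, and add a label-permutation p value.
- Refit the final model on all children, and keep the hold-out result as secondary, shown as a count with an exact interval.
- Temper the claims of discriminating ability in the Abstract's Conclusions and in the Discussion to match the resulting interval.

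The cost is computing time, a final refit, an estimate that describes the modelling procedure as a whole, and probably an accuracy below 0.85. No further children are needed.

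### The tuning metric is micro-F1, which is accuracy under another name; Table 3 prints it as F1 while Table 4 uses ADHD-class F1, and the choice of SVM depends on which metric is meant

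*Protocol article*

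**What the plan says.** The ML Methodology section names the criterion twice. One paragraph gives no averaging: "The *F1* score is used as the optimization criterion in the 3-fold CV". A later one is specific: "The objective of the optimization is to maximize the micro-*F1* score across all validation folds". The selection rule is that "the algorithm with the best-performing pipeline in the 3-fold CV is selected as the proposed method".

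In Results, Gameplay Data, the first reason for choosing SVM is "It achieves the highest validation *F1* score (0.66"). The second reason concedes a tie: "Although SGD achieves the same validation score as SVM, the latter also achieves a better fit". Here fit means the difference between training and validation scores, about +0.07 for SVM and about -0.09 for SGD. The same section says that most classifiers passed an F1 of 0.5, and it places logistic regression (LogReg) with SGD, SVM and the passive aggressive classifier (PAC) as superior to the rest. Table 3 gives the cross-validation results and Table 4 the test results; both have columns headed F1.

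**The concern.** A reader takes F1 to be a measure that is low when a classifier misses the ADHD children. Micro-F1 in a two-class problem does not have that property: a model that never predicts ADHD scores the proportion of non-ADHD children. If Table 3's F1 is accuracy and Table 4's is not, the two tables cannot be compared, and the statements in Gameplay Data that rely on F1 rest on the wrong label.

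The stake is the headline. The Abstract reports accuracy of up to 0.85, which is the SVM test result. The model tied with SVM in cross-validation has test accuracy 0.42, and the best test accuracy among the other seven methods is 0.57. Which metric and which tie-break apply decides which figure belongs to the proposed method.

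**Working it through.** **1. Micro-F1 equals accuracy.** Pool over both classes. Correct calls are TP + TN. Each false positive for one class is a false negative for the other, so pooled false positives and pooled false negatives are both FP + FN. Then

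micro-F1 = 2(TP + TN) / [2(TP + TN) + 2(FP + FN)] = (TP + TN) / N = accuracy.

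**2. The printed figure reproduces only as accuracy.** In Table 3 the F1 and accuracy columns agree to four decimals in all 8 rows, for training and validation. SVM and SGD both show 0.6667 in both columns. LogReg shows precision 0, recall 0 and F1 0.5714; its ADHD-class F1 is 0.

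**3. Table 4 uses another F1.** Naïve Bayes (NB) has accuracy 0.42, precision 0.42, recall 1.00 and F1 0.60. Taking 0.42 as 3/7, 2 × (3/7) × 1 / (3/7 + 1) = 0.60. This is ADHD-class F1 and differs from accuracy.

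**4. ADHD-class F1 for Table 3**, as 2PR/(P + R) from the printed validation precision P and recall R:

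| Method | P | R | Printed F1 | 2PR/(P+R) |
|---|---|---|---|---|
| SGD | 0.5667 | 1.0000 | 0.6667 | 0.723 |
| NB | 0.5556 | 0.7778 | 0.6190 | 0.648 |
| PAC | 0.5000 | 0.8889 | 0.5714 | 0.640 |
| SVM | 0.5833 | 0.6667 | 0.6667 | 0.622 |
| kNN | 0.4500 | 0.5556 | 0.5238 | 0.497 |
| RF | 0.4444 | 0.5556 | 0.5238 | 0.494 |
| RC | 0.3833 | 0.5556 | 0.4286 | 0.454 |
| LogReg | 0 | 0 | 0.5714 | 0 |

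Four of 8 exceed 0.5, against 7 of 8 on the printed column. LogReg is last and SVM is fourth.

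**5. Fold-level check.** Table 3 averages over folds, so step 4 is an approximation. The printed values fit 3 folds of 7 (3 ADHD, 4 non-ADHD), that is 21 participants: 0.5714 = 12/21 and 0.6667 = 14/21. Listing every set of fold counts that matches the printed accuracy, precision and recall gives one solution for SGD (TP 9 of 9, FP 7 of 12). For SVM there are three, all with TP 6 of 9 and FP 4 of 12.

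| Validation metric | SGD | SVM | Favours |
|---|---|---|---|
| Accuracy = micro-F1 | 14/21 = 0.667 | 14/21 = 0.667 | tie |
| ADHD-class F1, fold mean | 0.722 | 0.610-0.619 | SGD |
| ADHD-class F1, pooled | 18/25 = 0.720 | 12/19 = 0.632 | SGD |
| Balanced accuracy | (9/9 + 5/12)/2 = 0.708 | (6/9 + 8/12)/2 = 0.667 | SGD |
| Macro-F1, fold mean | 0.650 | 0.654-0.661 | SVM |
| Macro-F1, pooled | (0.720 + 0.588)/2 = 0.654 | (0.632 + 0.696)/2 = 0.664 | SVM |
| Weighted F1, fold mean | 0.640 | 0.660-0.667 | SVM |
| Weighted F1, pooled | 0.645 | 0.668 | SVM |

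Pooled non-ADHD F1 is 10/17 = 0.588 for SGD and 16/23 = 0.696 for SVM. Weighted F1 uses weights 9/21 and 12/21.

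**6. Test results (Table 4).** SGD: accuracy 0.42, F1 0.33. SVM: accuracy 0.85, F1 0.85.

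**The case against.** Much is already disclosed. The Methods say micro-F1 outright, and the unqualified mention can be read as shorthand for it. Table 3 follows that definition, on which SVM is joint best, so calling its score the highest is true though shared. Gameplay Data admits the tie and Table 4 prints both test results. The tie-break uses only training-set data, as the Methods require of modeling decisions. All of this stands.

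A reader might go further and infer that proper F1 selects SGD, so that the true headline is 0.42. The documents do not support that. The Methods never specify ADHD-class F1 for tuning, and two other standard versions, macro and weighted, put SVM first. The pipelines were tuned on micro-F1; retuning could change hyperparameters, ranking and test scores. SGD's lead comes from recall 1.00 with 7 of 12 controls misclassified, so ADHD-class F1 is not a clearly better guide here. A reader might also infer that the tie-break was chosen after the test scores were seen; nothing in the article shows that.

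The harm from class imbalance should not be overstated either: the inferred split is 9 to 12, and the all-non-ADHD model was not selected.

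None of this removes the labelling fault, the statements that depend on it, or the lack of a tie-break in the Methods.

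**Conclusion.** The concern holds in this form: one name covers two metrics, and the Gameplay Data text draws conclusions that fail on the F1 used in Table 4. On that F1, half the classifiers exceed 0.5, which is not most; LogReg, at 0, does not belong among the better models; and SVM, at about 0.62, is not the highest. On micro-F1 the Methods' rule gives a tie at 0.6667 and does not say how to break it. The choice between a test accuracy of 0.85 and one of 0.42 therefore depends on a metric and a tie-break that the Methods do not clearly fix. It does not follow that SGD is the right model or that 0.42 is the right headline; 0.42 only re-scores the printed table.

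Steps 1 to 4 need only the printed tables. Step 5 assumes 21 training participants (9 ADHD, 12 non-ADHD), inferred from the printed values, whereas Gameplay Data states 22 training and 8 test participants. Table 4's 0.42, 0.57 and 0.85 likewise fit sevenths (3/7, 4/7, 6/7) and not eighths. These counts need reconciling.

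**What to change.** - In ML Methodology, name one explicitly defined, class-aware criterion for both tuning and selection, for example ADHD-class F1 (which matches Table 4) or balanced accuracy, and use the same name throughout.
- State a tie-break. Fix both before the test set is opened. Because Table 4 is already published, the choice for the present data should be argued from the purpose of the tool and not from the test scores.
- Re-run tuning and selection with that criterion.
- Relabel Table 3's F1 columns as accuracy and add ADHD-class F1.
- Correct the three Gameplay Data statements: the count above 0.5, the standing of LogReg, and the first reason for SVM.
- Beside the headline 0.85, say that the model tied with SVM in cross-validation scored 0.42 on the test set.

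The cost is one re-run of the grid search, edits to one table and a few sentences, and possibly a less favourable headline.

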**Figure 2 figure2:**
[figure not shown]
Cross-Validation F1 scores. SGD: stochastic gradient descent.

**Table 3 table3:** Cross-validation results.

Method	Accuracy		Precision			Recall			*F1*	
	Training	Validation	Training	Validation	Training		Validation	Training		Validation
NB^a^	0.7619	0.6190	0.7011	0.5556	0.8333		0.7778	0.7619		0.6190
k-NN^b^	0.7619	0.5238	0.7083	0.4500	0.7778		0.5556	0.7619		0.5238
LogReg^c^	0.5714	0.5714	0.0000	0.0000	0.0000		0.0000	0.5714		0.5714
PAC^d^	0.6190	0.5714	0.5337	0.5000	0.8333		0.8889	0.6190		0.5714
RF^e^	0.6667	0.5238	0.5935	0.4444	0.7222		0.5556	0.6667		0.5238
RC^f^	0.6667	0.4286	0.6074	0.3833	0.6667		0.5556	0.6667		0.4286
SGD^g^	0.5714	0.6667	0.4932	0.5667	0.6667		1.0000	0.5714		0.6667
SVM^h^	0.7381	0.6667	0.7238	0.5833	0.6667		0.6667	0.7381		0.6667

^a^NB: naïve Bayes.

^b^k-NN: k-nearest neighbors.

^c^LogReg: logistic regression.

^d^PAC: passive aggressive classifier.

^e^RF: random forest.

^f^RC: ridge classifier.

^g^SGD: stochastic gradient descent.

^h^SVM: support vector machine.

**Table 4 table4:** Evaluation of test results.

Method	Accuracy		Precision			Recall			*F1*	
	CI	Test	CI	Test	CI		Test	CI		Test
NB^a^	0.14-0.85	0.42	0.14-0.85	0.42	1.00-1.00		1.00	0.25-0.92		0.60
k-NN^b^	0.14-0.71	0.42	0.00-1.00	0.33	0.00-1.00		0.33	0.00-0.67		0.33
LogReg^c^	0.14-0.85	0.42	0.14-0.85	0.42	1.00-1.00		1.00	0.25-0.92		0.60
PAC^d^	0.13-0.71	0.28	0.13-0.75	0.33	0.23-1.00		0.66	0.23-0.83		0.44
RF^e^	0.28-0.85	0.57	0.15-1.00	0.50	0.23-1.00		0.66	0.23-0.90		0.57
RC^f^	0.27-0.85	0.57	0.00-1.00	0.50	0.00-1.00		0.66	0.00-0.88		0.57
SGD^g^	0.14-0.71	0.42	0.00-1.00	0.33	0.00-0.76		0.33	0.00-0.66		0.33
SVM^h^	0.71-1.00	0.85	0.50-1.00	0.75	1.00-1.00		1.00	0.66-1.00		0.85

^a^NB: naïve Bayes.

^b^k-NN: k-nearest neighbors.

^c^LogReg: logistic regression.

^d^PAC: passive aggressive classifier.

^e^RF: random forest.

^f^RC: ridge classifier.

^g^SGD: stochastic gradient descent.

^h^SVM: support vector machine.

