## Discussion

Limitations of the existing screening procedures for ADHD diagnosis are summarized as high dependence on pen-and-paper practices, subjectivity bias, difficulty in monitoring in different settings, and risk of data loss. The ADHD360 platform, consisting of the serious game “Pizza on Time” and the mADHD360 app, attempts to offer a holistic technological solution for early detection of ADHD characteristics and serve as a training tool against ADHD-related symptoms. It facilitates real-time data collection in different settings and from different individuals involved in the user’s care. Moreover, the ADHD360 platform enables quantitative data analysis assessing the behavior and game performance of the user while providing a more integrated view of the user's behavioral characteristics. Investigating different state-of-the-art ML methods revealed that our platform is characterized by a notable capacity to discriminate players based on their in-game patterns as those who have ADHD characteristics and those who do not. Thus, it is expected to serve as a complementary screening tool benefiting health care professionals, educators, and people with ADHD.

However, the health emergency imposed by COVID-19 affected the implementation of pilot trials by forcing adaptation of the protocol to remote conditions. Moreover, lockdowns and social distancing may have contributed to the low sample size and the high number of dropouts during the study. Additionally, the long duration of the experimental protocol and the need for commitment to the study procedures may have negatively affected users’ adherence to pilot trials. Moreover, ADHD has been characterized by “a dislike of mental effort” [45]. Considering the aforementioned limitations, we recruited about twice as many participants as originally intended. However, the dropout rate was approximately 30% (13 participants), as 30 participants (70%) completed the first part of pilot phase remotely.

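### The fixed metric list omits specificity, so the false-positive rate that a screening claim needs is never reported

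*Protocol article*

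**What the plan says.** The ML Methodology section names the reported measures: "we report the performance metrics of accuracy, precision, recall, and" F1 scores. For tuning it states: "The objective of the optimization is to maximize the micro"-F1 score across the validation folds. On the held-out data it says that "the test set is used only to evaluate and report the statistics of the algorithm’s performance".

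Under Gameplay Data, performance is evaluated on "a test set consisting of data gathered from 8 (27%) participants using point estimates and CIs". Table 4 ("Evaluation of test results") and Table 3 (cross-validation) give exactly the four listed measures. The article gives no specificity, false-positive rate, area under the curve or confusion matrix.

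The Discussion concludes of the platform that "it is expected to serve as a complementary screening tool". The abstract gives accuracy up to 0.85 as the main result and concludes that the platform discriminates well between ADHD and non-ADHD play.

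**The concern.** Discrimination has two sides: the share of affected children detected, and the share of unaffected children wrongly flagged. Recall gives the first. Nothing in the list gives the second directly. Precision, recall and ADHD-class F1 do not count true negatives at all. Accuracy counts them only mixed with true positives.

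A classifier that calls every child ADHD can therefore show perfect recall and a middling F1, and the reader is not told that it separated nobody. A statement about screening use needs the false-positive rate and its uncertainty beside it, and here neither is shown.

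This is not detail that a condensed article leaves to a fuller document. The metric list is stated, and both results tables follow it.

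**Working it through.** **1. Naïve Bayes and logistic regression on the test set (Table 4).** Both have accuracy 0.42, precision 0.42, recall 1.00 and F1 0.60. Recall 1.00 means FN = 0. Taking accuracy as equal to precision:

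TP/(TP+FP) = (TP+TN)/(TP+FP+TN)

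Cross-multiplying and cancelling leaves TN × FP = 0. Precision below 1 means FP > 0, so TN = 0. Both models labelled every test child ADHD. This algebra does not use the test-set size. It does take the two printed values of 0.42 as exactly equal, which step 2 supports.

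**2. Counts behind Table 4.** All integer 2×2 tables for test sizes 5 to 15 and every class split were matched to the four printed measures, rounded or truncated to two decimals. All eight rows fit 7 children (3 ADHD, 4 non-ADHD), or exactly double that, 14. No row fits 8. For example, an accuracy of 0.42 lies between 3/8 = 0.375 and 4/8 = 0.50, whereas 3/7 = 0.428 truncates to 0.42.

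| Model | TP, FP, FN, TN | F1 = 2TP/(2TP+FP+FN) | Sensitivity | Specificity | Balanced accuracy |
|---|---|---|---|---|---|
| SVM | 3, 1, 0, 3 | 6/7 = 0.857 (printed 0.85) | 3/3 | 3/4 | 0.875 |
| Naïve Bayes, logistic regression | 3, 4, 0, 0 | 6/10 = 0.60 (printed 0.60) | 3/3 | 0/4 | 0.500 |
| Random forest, ridge | 2, 2, 1, 2 | 4/7 = 0.571 (printed 0.57) | 2/3 | 2/4 | 0.583 |
| k-NN, SGD | 1, 2, 2, 2 | 2/6 = 0.333 (printed 0.33) | 1/3 | 2/4 | 0.417 |
| PAC | 2, 4, 1, 0 | 4/9 = 0.444 (printed 0.44) | 2/3 | 0/4 | 0.333 |

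**3. Exact (Clopper-Pearson) 95% intervals for the selected SVM.**
- Sensitivity 3/3: lower limit 0.025^(1/3) = 0.29, upper limit 1.00. Table 4 prints 1.00-1.00, an interval of no width from three children.
- Specificity 3/4: 0.19 to 0.99. The false-positive rate is 1/4, or 25%, with interval 0.01 to 0.81 by subtraction.

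**4. Cross-validation (Table 3).** F1 equals accuracy in every row, as micro-F1 does. In Table 4 it does not (0.60 against 0.42), so F1 there is the ADHD-class value. All eight validation accuracies are multiples of 1/21 (13, 11, 12, 12, 11, 9, 14 and 14 twenty-firsts, in table order), which suggests 21 children, 9 ADHD and 12 non-ADHD. The text says 22. Assuming 21, in three folds of 3 ADHD and 4 non-ADHD:
- SVM: recall 0.6667 = 6/9. Accuracy 0.6667 = 14/21, so TN = 14 − 6 = 8 and specificity is 8/12. Fold precisions of 2/4, 1/2 and 3/4 average to the printed 0.5833.
- SGD: recall 1.0000 = 9/9. Accuracy is also 14/21, so TN = 14 − 9 = 5 and specificity is 5/12. Fold precisions of 3/5, 3/5 and 3/6 average to the printed 0.5667.

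The two tie at 0.6667 on the selection score. One flags 4 of 12 unaffected children and the other 7 of 12. Gameplay Data breaks the tie on the gap between training and validation scores and does not mention this difference.

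**The case against.** The four measures are a conventional set, and this is a pilot whose authors call the analysis preliminary and ask for more data. Accuracy, precision and recall together determine the false positives, which is how the working recovers them. The low accuracy and precision of naïve Bayes and logistic regression already mark them as weak. All of that stands, and it limits the point to one of reporting.

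Several stronger readings are tempting but not supported:
- *The metrics reward over-calling ADHD.* Tuning and selection use validation micro-F1, which equals accuracy. At 9 against 12 children, calling everyone ADHD scores 9/21 = 0.43 and calling no one ADHD scores 12/21 = 0.57. Logistic regression in Table 3 (recall 0.0000, F1 0.5714) did the latter.
- *The order of models on test F1 drove a decision.* The SVM was chosen on cross-validation results. The test set was for evaluation only, and the SVM also leads there on accuracy and balanced accuracy.
- *F1 ranks uninformative models above informative ones.* Random forest and ridge, at 2/3 and 2/4, have the single most probable table under no association (two-sided Fisher p = 1). They cannot be called informative.
- *The false-positive rate cannot be estimated.* It can be back-calculated; it is simply not reported.
- *Everything would look worse.* SVM balanced accuracy is (1.00 + 0.75)/2 = 0.875, no lower than the printed 0.85.

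Nor does the SGD comparison show that SGD should have been chosen: its test results are worse. Whether false positives matter more than missed cases is not settled either, since the Literature Summary raises both over- and underdiagnosis.

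**Conclusion.** The point holds as a reporting weakness that bears on interpretation. The fixed metrics leave the false-positive rate unreported, while the abstract and Discussion make claims that depend on it. Two of the eight classifiers labelled every test child ADHD and still show a test F1 of 0.60. For the selected SVM the implied specificity is 3/4, with an exact interval of 0.19 to 0.99. That is too wide to support an unqualified screening statement.

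The test-set counts are inferred. They rest on 7 test children, which reproduces every Table 4 row, whereas the stated 8 reproduces none. Fourteen would give the same proportions with narrower intervals but is further from the text. The cross-validation counts rest on 21 children where the text says 22, so they illustrate how the selection score hides a trade-off and are not firm estimates. The choice of the SVM is not called into question.

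**What to change.** - In ML Methodology, add specificity to the listed measures and name recall as sensitivity.
- In Tables 3 and 4, give the confusion counts, sensitivity and specificity for each classifier, and add balanced accuracy beside F1. State which F1 each table uses.
- For the test set, give exact binomial intervals, which also replaces the 1.00-1.00 interval for recall. Exact intervals are not proposed for cross-validation, because predictions pooled from three fold-specific models are not a simple binomial sample.
- Reconcile the stated 22 training and 8 test children with the 21 and 7 that the tables imply.
- In the abstract and Discussion, qualify the screening statement by the SVM specificity and its interval.

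The cost is a little recomputation from predictions already held, and an interval that is visibly wide. No new participants or data are needed.
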